#### Socialization/health education (SHE) sessions

The interactive SHE sessions (intervention group only) will begin with a physical activity goal-setting session while the subject matter of the remaining nine SHE sessions topic areas will be decided upon by trial participant consensus. As for the WTL program [28], these sessions will, for the most part, be developed and facilitated by the students although some invited speakers will facilitate sessions in their area of expertise.

#### Exercise and walking sessions

A certified YMCA trainer will facilitate the 1-h exercise and 30-min walking-track sessions. These sessions will follow the standardized YMCA Fit for Life 50+ Program (https://www.h2okelowna.ca/Programs/Health-Fitness/Land-Fitness/Fit-for-Life-50?location=13ee95d3-cc67-48ca-9adb-c05d2d27fdc4) designed to build up strength, movement, coordination and balance. It incorporates TRX™, free weights and the walking track. Participants who miss an exercise session are asked to “make each one up” by either attending another Fit for Life 50+ Program session or doing a set of home-based Otago Falls Prevention Program exercises [37]. Participants are also encouraged to walk between trial sessions and will be provided a pedometer and tracking sheets to motivate and encourage them.

The interactive GAR and SHE sessions will begin with structured goal-setting interviews based on the model of social cognitive theory of behavior change [38], motivational interviewing [39] and collaborative goal setting [40]. Two to three specific, measurable, achievable, realistic goals for both auditory and physical activity outcomes will be identified and prioritized by participants. Goal setting and attainment will be revisited at each session using the social cognitive approach to motivate, empower and encourage adherence.

### Measures

The primary measures: feasibility outcomes and acceptability of the pilot RCT:Recruitment strategies (how did participants hear of the trial, willingness of hearing clinics to recruit participants, number of potential participants contacting the research team and by consulting the pilot trial participants, optimal ways to reach out to isolated individuals with HL)Recruitment rates: numbers of potential participants that contact the trial center; of those, how many participated in telephone interview, how many gave verbal consent, and completed functional physical fitness testing and baseline questionnairesEligibility: how many potential participants were eligible, how many injuries, adverse events or dropouts)Randomization: acceptability/willingness to be randomized, how baseline measures compared between groupsSession adherence and overall retention rates (intervention versus control groups’ daily sign in sheets), final questionnaire completion rates and discontinuation rates (and reasons if given)Overall acceptability of the program (control versus intervention) and GAR, SHE and exercise components (participant evaluation questionnaire: Likert-style and open-ended questions)What aspects need to change? What should those changes be and how?Acceptability of student participation in the HE and GAR sessions; capacity for student trainees – benefit to research and community? Role or impact of older adult/student relationship might be something to measure in relation to loneliness…Acceptability and capacity of the YMCA to host the definitive RCTCost recovery processes for the YMCA: need to fund YMCA space, staff and time for budgeting purposes

The secondary measures: participant-specific outcomes (defined below) in order to generate estimates of data variation (standard deviations (SDs), standard error of the means (SE)), 95% confidence intervals (CIs) around the differences between control and intervention groups, and to determine the sample size estimate for the primary outcome of the definitive RCT:Questionnaire measures:data collected at initial assessment include: age, sex, living situation (alone or with someone), marital status, ethnicity, highest level of education, annual household income before taxes, employment status, use of mobility or balance aids, falls over the previous 3 months, and HA useFunctional fitness measures:measures taken at initial assessment and at the end of the 10-week intervention will include a battery of tests found to be reasonable estimates of the level of fitness associated with remaining physically mobile and independent in later life [41]. All assessments will be conducted over the 1-week period immediately before and at the end of the trial at the same locale using the same protocol and instruments. With the exception of the 6-min Walk Test (6MWT), all tests will be repeated twice for each limb (as appropriate) and the better of the two measures will be recorded (for each limb as appropriate).Muscular endurance of the lower limbs will be assessed using the 30-s Chair Stand Test (30SCST) [42]Aerobic fitness using gait speed in a 6MWT [43]Agility and balance using the Timed Up and Go Test (TUGT) [43]Grip strength (isometric muscular strength of the hand and forearm) [44] using a Smedley handgrip dynamometer (Fabrication Enterprises, Elmsford, NY, USA)The One-foot Balance Test [45] to examine balance and leg strength/enduranceFlexibility (lower limbs and lumbar spine) using the Chair Sit and Reach Test [46]; the Back Scratch Test to assess the general shoulder range of motion [41]
Measures of hearing and health-related quality of life: (ICF outcomes: activities limitations, participation restrictions) at initial and end of intervention will include:The Hearing Handicap Inventory for the Elderly (HHIE-25) [47], a validated 25-item questionnaire assessing the social, emotional and psychological challenges associated with HL and correlates well with audiometrically measured moderate to severe HLThe RAND SF-36 [48] (ICF outcomes: physical function, activities limitations, participation restrictions, a 36-item health-related quality of life measure with eight subscales including physical functioning, role functioning, bodily pain, general health, vitality, mental health, emotional role limitation and social functioning and social support
Measures of loneliness and social connectedness at initial and end of intervention:De Jong-Gierveld Loneliness Scale [49])Social participation using eight items developed for the Canadian Community Health Survey 4.2 [50], to determine the frequency of participation in family, friendship, and activities with other people outside of the householdAvailability of social support using the Medical Outcomes Trial-Social Support Survey [51], a validated scale of overall social support and four domains of social support (emotional/informational, tangible, affectionate and positive interactions)The Geriatric Depression Scale, a15-item questionnaire used as a screening tool in the older population [52]
Blood pressure and heart rate (initially and at end of intervention) according to Canadian Hypertension Education Program guidelines [53] using the validated BPM-100 (BpTRU Medical Devices, Coquitlam, BC, Canada), an automated oscillometric noninvasive blood pressure monitorMeasures taken at the end of the trial.GAR evaluation: at end of intervention. The International Outcomes Inventory-Alternative Interventions (IOI-AI) [54] questionnaire to determine outcomes of GAR programs. A modified Client Oriented Scale of Improvement (COSI) questionnaire [26] to evaluate the extent to which individual goals were reached [55] and overall benefit of the GAR intervention

### Serious adverse events

The trial is expected to be low risk for serious adverse events, such as cardiovascular events (myocardial infarction, stroke, etc.), given the validated PARQ+ screen and/or the provision of a physician signed letter of “exercise readiness.” While the risk is low, there is a possibility of a fall and or fracture during the supervised exercise sessions. This risk will be minimized with exercise sessions facilitated by Canadian Society for Exercise Physiology (CSEP) certified fitness trainers. If an adverse event does occur, the PI (clinical team member onsite during all session times) and key YMCA staff will be immediately alerted and, research protocols and institute appropriate procedures initiated and changes to the exercise program implemented if deemed necessary.

#### Sample size

The sample size for this pilot trial [56, 57] is based upon anticipated numbers of potential participants who contact the trial center within an 8-week recruitment period. Based on previous unpublished experience in the WTL program using pre-post data on older adults with HL, we estimate that approximately 15 per week will contact the trial center, 50–60% of those who make initial contact will meet the eligibility criteria and agree to be randomized, and at least 23 people per group at trial end to show a clinically meaningful average increase in the Sit to Stand Test (STS) of 2 [58]. This sample size will also ensure that enough data is available to generate reliable SE, SD and 95% CI on the sample size required for the large RCT with this measure as the primary outcome. A definitive RCT will be deemed feasible when at least 120 individuals contact the pilot trial center, ≥90% fulfill feasibility outcomes 2–4 and at least 70% of randomized participants fulfill outcome number 5. A larger RCT will be deemed acceptable if at least 85% of participants find the GAR, exercise and SHE sessions highly acceptable or acceptable.

#### Research data and management

Participants will be assigned a participant number upon initial contact with the trial coordinator. Questionnaire and functional fitness testing data will be collected and recorded by the trained research team members on paper-based data collection sheets during the week prior to randomization and during the week after the end of the 10-week trial. Fully anonymized data will be manually entered into an Excel® spreadsheet, 100% double-checked for errors or omissions by a team member blinded to the participants’ group allocation, then cleaned and transferred into Stata® statistical software for analysis.

#### Statistical methods

For primary outcome measures, analyses will be descriptive and variables will be expressed as frequency and percentage for all data relating to recruitment, adherence, overall retention rates, plus all other categorical data on program feasibility and acceptability. Any continuous data will be expressed as mean plus SD or median and interquartile range (for non-normal data). Participant demographics at baseline will be described both by group and overall sample. Responses for Likert-type data will be combined into three nominal categories (“strongly agree/agree,” “strongly disagree/disagree” and “don’t know”) and differences between the intervention and control groups analyzed by Fisher’s exact test [59]. Responses to open-ended questions will be coded and organized into themes and descriptive statistics (including percentages) will be used to report the results.

For secondary outcomes measures, the main analysis will be intention-to-treat: the group to which a participant is assigned will be the group in which they are analyzed, regardless of participant protocol violations, attendance rate or dropout [60]. Last observation carried forward will be used to impute missing outcome data assuming less than 20% missing data for a given outcome measure. The functional fitness measures will be analyzed using the analysis of covariance method with the baseline measure as the covariate and follow-up measure as the outcome [61]. Data will be transformed for analysis of covariance when initial and end of intervention data is non-normal. Both a complete case and per protocol analysis will also be conducted to study the impact of departures from the assumptions made in the main intention-to-treat analysis. All continuous primary and secondary outcome variables will be assessed for normality visually using histograms and boxplots, with the Shapiro-Wilk test used as a supplement to the graphical assessment.

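### With only a baseline and one follow-up, last observation carried forward scores every missing outcome as no change, which distorts the effect, its interval and the SD meant for planning, even below the 20% limit

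*Protocol article*

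**What the plan says.** Statistical methods makes intention-to-treat the main analysis of the secondary outcomes, with participants kept in their assigned group "regardless of participant protocol violations, attendance rate or dropout". For missing values it states: "Last observation carried forward will be used to impute missing outcome data assuming less than 20% missing data for a given outcome measure". Functional fitness is analysed by the "analysis of covariance method with the baseline measure as the covariate and follow-up measure as the outcome". As a check, "Both a complete case and per protocol analysis will also be conducted to study the impact of departures" from the assumptions of the main analysis.

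Measures describes the fitness tests as "measures taken at initial assessment and at the end of the 10-week intervention" and adds: "All assessments will be conducted over the 1-week period immediately before and at the end of the trial". Research data and management confirms two collection points, "during the week prior to randomization and during the week after the end of the 10-week trial". No outcome assessment in between is described.

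Measures also gives the purpose of the secondary outcomes: estimates of SD, SE and the 95% CI for the group difference, and a sample size for the definitive trial. Sample size repeats this for the Sit to Stand Test, where a mean increase of 2 is the target, and asks for "at least 23 people per group at trial end".

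**The concern.** Carrying forward needs an earlier post-baseline value to carry. Here there is none, so a participant without a follow-up is entered with follow-up equal to baseline and is then treated as fully observed. Three consequences follow.

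- The difference between arms mixes the real change in completers with an assigned change of zero in everyone else.
- The standard error is computed as if all 60 outcomes had been measured.
- The residual variance is that of a mixture of real and assigned values.

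Zero change also sits badly with the protocol's own expectations. Background reports promising fitness gains by programme end among earlier participants with hearing loss, and Sample size targets a gain of 2 stands. Dropout may well differ by arm: under Intervention, one arm attends twice a week for 2.5 hours (1 hour plus 90 minutes) and the other once a week for 1 hour. At stake are the effect estimate, interval and SD that will be used to design the larger trial.

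**Working it through.** **Inputs from the protocol.** 60 randomized (Trial design); target difference 2 stands and at least 23 per group at the end (Sample size); two assessments; ANCOVA on baseline; LOCF below 20% missing.

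**Assumptions.** 30 per arm (no ratio is stated), SD σ = 3.3, baseline to follow-up correlation ρ = 0.7, dropout at random. The protocol gives no SD, correlation, alpha or power, so its figure of 23 per group can be neither reproduced nor refuted.

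**Room under the 20% limit.** 20% of 60 is 12, so the rule covers up to 11 missing. The examples below stay inside it: 3 + 3 (10%), 5 + 5 (16.7%), and 8 + 3 = 11 of 60 (18.3%).

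**Effect.** Let c be the mean change in controls, e the true effect, and d_I and d_C the missing shares in the intervention and control arms. Each missing participant contributes zero change, so

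expected LOCF effect = (1 − d_I)(c + e) − (1 − d_C)c.

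- 10% in each arm, e = 2: 0.9 × 2 = 1.80.
- 16.7% in each arm, e = 2: (25/30) × 2 = 1.67.
- 8 v 3 of 30, c = 2, e = 2: (22/30) × 4 − (27/30) × 2 = 2.93 − 1.80 = 1.13.
- 8 v 3 of 30, c = 2, e = 0: (22/30) × 2 − (27/30) × 2 = −0.33.
- Reversed, 3 v 8 of 30, c = 1, e = 2: (27/30) × 3 − (22/30) × 1 = 2.70 − 0.73 = 1.97, almost no bias.

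**Residual variance.** With m the true mean change in an arm and d its missing share, the arm's variance about the fitted line is

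(1 − d)σ²(1 − ρ²) + d(1 − d)(1 − ρ)²σ² + d(1 − d)m².

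The true value is σ²(1 − ρ²) = 10.89 × 0.51 = 5.55, an SD of 2.36. At d = 1/6 the first two terms are 4.63 + 0.14 = 4.76.

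- No control change (m = 0 and 2, mean m² = 2): 4.76 + 0.139 × 2 = 5.04, SD 2.25, too small.
- Both arms gain 2 and the effect is 2 (m = 2 and 4, mean m² = 10): 4.76 + 0.139 × 10 = 6.15, SD 2.48, too large.

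**Simulation under the same assumptions.**

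| Missing (of 30 v 30) | c | e | LOCF effect | LOCF 95% coverage | Observed-data ANCOVA |
|---|---|---|---|---|---|
| 3 v 3 | 0 | 2 | 1.80 | 94% | 2.0, about 95% |
| 5 v 5 | 0 | 2 | 1.66 | 92% | 2.0, about 95% |
| 8 v 3 | 2 | 2 | 1.13 | 78% | 2.0, about 95% |
| 8 v 3 | 2 | 0 | −0.33 | 93% (type I error about 7%) | 0.0, about 95% |

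In the 5 v 5 case with no control change, the LOCF standard error is 0.58 against 0.67 from observed data. The difference is precision credited to values nobody measured. A separate simulation with SD 3 and correlations from 0.5 to 0.85 gave the same picture: effects of 1.65 to 1.67 and coverage of 89% to 92% at 16.7% missing.

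**Illustrative sample size of the definitive trial** (90% power, two-sided 5%, both assumed): n per arm = 2(1.96 + 1.2816)² SD²/δ² = 21.0 × SD²/δ².

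- True SD, δ = 2: 21.0 × 5.55/4 = 29.2, so 30.
- LOCF SD without control change, δ = 2: 21.0 × 5.04/4 = 26.5, so 27.
- LOCF SD when both arms gain 2, δ = 2: 21.0 × 6.15/4 = 32.3, so 33.
- LOCF SD without control change and the LOCF effect (1.67² = 2.78): 21.0 × 5.04/2.78 = 38.1, so 39.

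**Can 20% be exceeded?** If 30 per arm shrink to 23, 7/30 = 23.3% are missing. The feasibility criterion of 70% on outcome 5 leaves up to 30%. Either would take an outcome beyond the LOCF condition.

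**The case against.** The strongest defence is that the damage is contained.

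- LOCF is confined to outcomes with less than 20% missing. With equal dropout and no control change, coverage there stays at 92% or more. That is right for that scenario, but the 8 v 3 case also lies inside the limit and is not mild.
- A complete-case analysis is already promised as a check on the assumptions, so an observed-data SD and CI will exist. That is also true, and it makes the remedy nearly free. As planned, though, the affected result remains the main one.
- The observed-data ANCOVA looks unbiased here because the simulation assumed random dropout. This stands: it relies on missing at random and is not assumption-free.

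Four stronger readings are tempting, and the documents do not support them.

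- *LOCF always makes the SD too small.* It can also make it too large, as shown above.
- *The definitive trial will therefore be too small.* The direction depends on the SD and on which effect is used: 27, 33 or 39 against 30.
- *The 20% condition fails on the plan's own numbers.* The 23 per group is a minimum, not a forecast. Outcome 5 combines session adherence with retention, questionnaire completion and discontinuation, so someone can fall short on it and still have a follow-up. The figures show only that 20% could be exceeded. A fallback rule for that case may stand in an analysis plan that is not shown, so its absence is not counted here.
- *The pilot's main purpose is undermined.* Feasibility and acceptability are primary, analysed descriptively, and the progression criteria use no imputed outcome.

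**Conclusion.** The point holds as a should-fix. With these two assessment times, the LOCF rule in the main analysis is baseline carried forward and assigns zero change to each missing outcome. Inside the rule's own limit it usually pulls the effect toward zero: by 10% to 17% with equal dropout and no control change, and from 2 to about 1.1 when the intervention arm loses more people and both arms improve. In the latter pattern a true null moves by about -0.3. Attenuation is usual but not universal, since heavier control dropout with a common gain can nearly cancel it. Interval coverage drops to about 92% to 94% in the mild cases and 78% in the adverse one. The SD is distorted in a direction that cannot be known beforehand.

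The sizes rest on 30 per arm, SD 3.3, correlation 0.7, random dropout and the stated common gains, none of which the protocol supplies. The mechanism rests on none of them.

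**What to change.** - Remove LOCF and its 20% condition from Statistical methods.
- Make the main analysis the baseline-adjusted ANCOVA on all randomized participants with an observed follow-up, analysed as allocated. This is the planned complete-case analysis moved into first place. Multiple imputation done separately by arm is an acceptable alternative.
- Take the SD, SE and 95% CI used to plan the definitive trial from that model.
- Add a delta-shift sensitivity analysis, in which missing participants are assumed to have done worse or better than predicted by stated amounts, by arm.

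The cost is a change of wording and a somewhat wider interval (standard error 0.67 in place of 0.58 in the 16.7% example), together with an explicit missing-at-random assumption, which the delta-shift analysis then tests.

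### With only two visits, last observation carried forward enters every missing final fitness test as exactly zero change, which biases the main ANCOVA and misstates its precision

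*Protocol article*

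**What the plan says.** Functional fitness is assessed twice. The Measures section describes "measures taken at initial assessment and at the end of the 10-week intervention will include a battery of tests", and Research data and management places the two assessments in the week before randomization and the week after the 10-week trial. No assessment in between is described.

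Statistical methods then fixes four things:

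- The analysis set: "For secondary outcomes measures, the main analysis will be intention-to-treat".
- The handling of missing outcomes: "Last observation carried forward will be used to impute missing outcome data assuming less than 20% missing data for a given outcome measure".
- The fitness model, an "analysis of covariance method with the baseline measure as the covariate and follow-up measure as the outcome".
- The side analyses: "Both a complete case and per protocol analysis will also be conducted to study the impact of departures from the assumptions".

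The secondary measures are collected "in order to generate estimates of data variation (standard deviations (SDs), standard error of the means (SE)), 95% confidence intervals (CIs" around the group differences, and to size the definitive trial. The Sample size section expects the pilot to "generate reliable SE, SD and 95% CI on the sample size required for the large RCT", with the Sit to Stand Test (STS) as that trial's primary outcome. Neither section says which analysis supplies these figures.

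**The concern.** Carrying the last observation forward is usually discussed for trials with several visits. Here the last value before a missing final test can only be baseline. The rule therefore sets follow-up equal to baseline and then regresses follow-up on that same baseline. Every imputed participant lies exactly on the no-change line, whatever the reason for leaving, and counts as a full observation.

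Two things follow. The estimated difference is biased by an amount that depends on how dropout splits between arms and on how much each arm truly changes. The standard error is computed as if the imputed values had been measured. The difference, its interval and its variability are the participant-level results the pilot is meant to pass on.

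**Working it through.** **Inputs from the article.** 60 randomized (Trial design), so 30 per arm if equal; a difference of 2 stands and at least 23 per group at trial end (Sample size); two measurement occasions; ANCOVA on baseline.

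**Assumed, because the article gives no figures.** STS SD S = 4, baseline to follow-up correlation r = 0.7, 11 of 60 missing (18%, inside the 20% condition), missing completely at random. c is the mean change in controls; dI and dC are the dropout fractions in the intervention and control arms.

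**The plan's own figures.** No SD, alpha or power is stated, so 23 per group can be neither confirmed nor refuted. Under 80% power and two-sided 5% it implies an SD of 2.42. The attrition it allows can be computed: 60 to 46 is 14/60 = 23.3%.

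**Effect.** With dropout unrelated to outcome, the LOCF difference has expectation (1 − dI)(c + 2) − (1 − dC)c.

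- Split 6/5 (intervention/control), c = 0: 0.80 × 2 = 1.60
- Split 9/2, c = 0: 0.70 × 2 = 1.40
- Split 9/2, c = 1: 0.70 × 3 − 0.933 × 1 = 1.17
- Split 2/9, c = 1: 0.933 × 3 − 0.70 × 1 = 2.10, larger than the truth

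**Residual variance.** With all 60 measured it is S²(1 − r²) = 16 × 0.51 = 8.16. Under LOCF, within an arm with dropout d and mean change m, it is (1 − d)·2S²(1 − r) + d(1 − d)m² − (1 − d)²(1 − r)²S². For the 6/5 split with c = 0:

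- Intervention: 7.68 + 0.64 − 0.92 = 7.40
- Control: 8.00 + 0 − 1.00 = 7.00
- Average: 7.20, which is 12% below 8.16

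The term in m² can reverse this. At S = 3, r = 0.8, c = 1 and the same split, the two arms give 4.09 and 2.89, average 3.49, against a true 3.24.

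**Standard error.**

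- All 60 measured: √8.16 × √(2/30) = 0.74
- Complete cases, 24 and 25: √8.16 × √(1/24 + 1/25) = 0.82
- LOCF: √7.20 × √(2/30) = 0.69, and 0.70 in simulation, where chance baseline imbalance adds a little

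LOCF thus reports more precision with 11 people missing than full follow-up would give.

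**Simulation check** (8,000 trials per row, S = 4, r = 0.7):

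| Split I/C | c | LOCF estimate | LOCF SE | LOCF coverage | Complete-case estimate | Complete-case coverage |
|---|---|---|---|---|---|---|
| 6/5 | 0 | 1.59 | 0.70 | 92% | 1.99 | 95% |
| 9/2 | 0 | 1.41 | 0.70 | 87% | 2.01 | 94% |
| 9/2 | 1 | 1.17 | 0.73 | 81% | 2.00 | 95% |
| 2/9 | 1 | 2.09 | 0.70 | 96% | 1.99 | 95% |

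**Consequence for sizing the definitive trial**, with n per arm = 2 × 7.85 × variance / difference² (80% power, two-sided 5%):

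- True variance, difference 2: 2 × 7.85 × 8.16 / 4 = 32.0, so 33
- LOCF variance, difference 2: 2 × 7.85 × 7.20 / 4 = 28.3, so 29
- LOCF variance and LOCF difference 1.6: 2 × 7.85 × 7.20 / 2.56 = 44.2, so 45

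The two errors pull in opposite directions.

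**The case against.** **The effect need not shrink, nor the SD fall.** A reader might infer that the rule always dilutes the difference and understates variability. It does not. Heavier control dropout with a control gain enlarges the effect, and a high correlation or small SD with a control gain inflates the residual variance. The raw follow-up SD hardly moves: at SD 3.5, correlation 0.7 and 19% equal dropout with no control change it is 3.54 against 3.50. This objection stands. It limits the claim about direction, but an error of unpredictable sign is no better in a main analysis.

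**The definitive trial is not handed a wrong SD.** A reader might also infer that it will be undersized. The article does not say so: it names no source for the planning figures, and the planned complete-case analysis could supply them. Undersizing follows only if the LOCF variance is paired with a fixed difference of 2; using the LOCF difference as well oversizes the trial. This stands too. What remains is that the source is unnamed and the analysis called main is the unsuitable one.

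**Complete-case analysis wins here by construction.** The simulation makes missingness random. Dropout through injury or decline could break that, and someone who stops exercising may truly gain nothing, so zero change could be near the truth for the mean. That is fair and is why the fix includes a scenario for dropouts who do worse. Even then, imputing zero change with no spread treats unmeasured people as measured.

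**The plan already protects itself.** It sets a 20% condition and adds complete-case and per-protocol analyses, so readers will see both estimates. This helps in part. The bias above arises at 18% missing, and the complete-case result is only a side check. The loss from 60 to 46 (23%) exceeds the condition, and the 70% criterion applied to session adherence and retention leaves room for 30%, yet no rule covers those cases.

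**Conclusion.** The concern holds in this form: with two visits the stated rule is baseline carried forward, and it enters missing participants in the main fitness analysis as observed zero change. That much comes from the text alone.

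The size rests on the assumed SD, correlation, random missingness and dropout split. In the nearly balanced base case with no control change, the estimate is about 20% too small (1.6 against 2.0), the standard error is about 15% below the complete-case value (0.70 against 0.82), and coverage is about 92%. With a 9/2 split coverage is 87%, or about 80% if controls gain 1 stand. The documents support neither a fixed direction nor a definite undersizing of the next trial.

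This should be fixed, but it does not threaten the pilot's purpose. The fitness measures are secondary, the primary feasibility outcomes are descriptive, and the progression criteria rest on contacts, eligibility, randomization, adherence, retention and acceptability.

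**What to change.** - Make the main fitness analysis an ANCOVA on all participants with an observed follow-up, in the arm assigned, adjusting for baseline and the randomization strata (gender and age group). Multiple imputation by arm from baseline variables is an alternative.
- Apply it at any level of missingness, which removes the gap at 20% and above.
- State that the SD, SE and 95% CI for the definitive trial come from this analysis.
- Keep baseline carried forward only as a labelled sensitivity scenario, beside a delta-shift scenario in which dropouts do worse than predicted. The observed-data analysis assumes missingness is ignorable given baseline, so that assumption needs a test.

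The cost is one paragraph of analysis text and a few lines of code, with no new data. The interval will usually be somewhat wider: in the base case the standard error goes from about 0.70 to 0.82, which reflects the information actually collected.
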